### Protocol deviations

As the trial is open-label, protocol deviations may occur. Furthermore, due to its noninferiority nature and the need for per-protocol analyses, protocol deviations will be followed closely and evaluated by the coordinating center in accordance with predefined criteria.

In the Antibiotic Therapy Group, protocol deviations will be considered if the patient does not receive antibiotics within 24 hours after randomization or if the patient receives less than seven days of antibiotic treatment, except for patients eligible for a shorter treatment duration (patients who have complete clinical improvement) who should receive at least five days of antibiotic treatment.

In the Watchful Waiting Group, antimicrobial initiation after randomization within the 7-day treatment protocol window will be considered a protocol deviation in the absence of another clear indication for antibiotic treatment initiation, as described above.

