### Sample size

The sample size calculation was based on the demonstration of noninferiority of the watchful waiting strategy compared to the use of antibiotics for 7 days strategy. A sample size of 295 patients per group (total of 590 patients), with a one-sided t test for noninferiority (with a significance level of 0.05), has 80% power to reject the null hypothesis that the number of VFDs at 28 days in the Watchful Waiting Group is inferior to the number of VFDs at 28 days in the Antibiotic Treatment Group for 7 days by a margin of 20% and a coefficient of variation of 1.38,^(7)^ considering a potential loss to follow-up or dropouts of 10%.

The choice of the 20% noninferiority margin was motivated by what was considered acceptable by the Steering Committee from a clinical perspective. This 20% noninferiority margin translates into a 1.5 VFD difference at 28 days, considering the mean VFD of 7.69 days and the standard deviation (10.67) in patients with VAT from a prior publication.^(7)^

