### Statistical analysis

The main analysis will follow the intent-to-treat framework, where the null hypothesis is that the number of VFDs up to 28 days in the Watchful Waiting Group is less than the number of VFDs in the Antibiotic Treatment Group for 7 days by a margin of 20%. If the upper bound of the 95% confidence interval for inferiority of the Watchful Waiting Group is < 20%, we will reject the null hypothesis of inferiority. To estimate the effect of treatment on the primary outcome, as well as in the interim analyses, an appropriate statistical model adjusted for stratification variables will be used for this type of outcome according to the variable behavior: either a generalized additive model for location scale and shape with zero-inflated beta distribution or nonparametric tests with the calculation of measures of effect and confidence intervals using resampling techniques (bootstrap) can be used. The effect size will be estimated according to the model best fitted to the data, with a 1-sided 95% confidence interval (95%CI) for noninferiority. If the noninferiority hypothesis is satisfied, superiority for the primary outcome will be tested considering a 95%CI using a hierarchical closed testing procedure. A primary sensitivity analysis of this noninferiority analysis will be a per-protocol analysis. Although per-protocol analyses are usually the primary analysis framework recommended for noninferiority trials, the intention-to-treat analysis framework may lead to more conservative estimates in antimicrobial trials.^(29)^ A p value of 0.05 will be considered to indicate statistical significance in the final analysis.

We also performed preplanned sensitivity analyses of the primary outcome, including only patients with microbiologically confirmed VAT, and we analyzed the randomization groups as an instrumental variable. Preplanned subgroup analyses will include the following: patients with or without a diagnosis of coronavirus disease 2019 (COVID-19) or other viral pneumonia, age ≤ 60 or > 60 years old, diagnosis of trauma on admission, acute brain injury, invasive mechanical ventilation duration of ≤ 5 or > 5 days at the time of randomization and effective vs. ineffective empirical antimicrobial treatment for isolated pathogens.

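### Read literally, the deviation rule counts death before the end of the antibiotic course as a protocol deviation in the antibiotic arm only, which can distort the per-protocol sensitivity analysis

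*Protocol article*

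**What the plan says.** The Protocol deviations section of the article sets a separate rule for each arm.

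- Antibiotic arm: apart from late initiation, there is a deviation "if the patient receives less than seven days of antibiotic treatment, except for patients eligible for a shorter treatment duration". The exempted patients are those with complete clinical improvement, who must still receive at least five days. Death and discharge are not mentioned.
- Watchful-waiting arm: "antimicrobial initiation after randomization within the 7-day treatment protocol window will be considered a protocol deviation in the absence of another clear indication". Nothing here depends on how long the patient survives.

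The same section gives the need for per-protocol analyses as a reason for tracking deviations. Under Statistical analysis, intention-to-treat is the main analysis, and "A primary sensitivity analysis of this noninferiority analysis will be a per-protocol analysis". Under Trial outcomes, anyone who dies by day 28 is scored as zero VFDs. The Discussion says that adjudicating deviations by such criteria is meant to reduce bias in the final analysis.

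The article does not define the per-protocol set. It leaves further detail on the sensitivity analyses to the statistical analysis plan, which is not available here.

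**The concern.** Take two patients who die on day 3, each managed exactly as assigned until then. The one in the antibiotic arm has had fewer than seven days of antibiotics and falls outside the single exception, so is a deviator. The one in the watchful-waiting arm has not deviated. Adherence therefore requires surviving the course in one arm and not in the other.

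Because death carries the lowest possible value of the primary outcome, dropping these deviators is selection on the outcome. It raises the antibiotic-arm mean with no treatment effect present. At stake is how the per-protocol result is read: it could appear to contradict an intention-to-treat finding of noninferiority that is in fact sound.

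**Working it through.** **Inputs.** From Sample size: 295 per group (590 in all), for 80% power at a one-sided level of 0.05; "by a margin of 20% and a coefficient of variation of 1.38"; an allowance of 10% for loss to follow-up or dropout; and a margin in days, "This 20% noninferiority margin translates into a 1.5 VFD difference at 28 days", which rests on a mean of 7.69 and an SD of 10.67 from an earlier study. From Trial outcomes: zero VFDs for deaths. Assumed, because the article gives no early mortality: the fraction q of the antibiotic arm who die before completing the course, taken as 2% to 15%.

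**The plan's own figure.** On the log scale for a ratio of means, σ² = ln(1 + 1.38²) = 1.066, so σ = 1.033, and the margin is −ln(0.8) = 0.223. Then n = 2 × (1.645 + 0.842)² × 1.066 / 0.223² gives 265 per arm, and 265/0.9 gives 295. The stated size reproduces, so nothing below depends on an arithmetic error in the plan. In days, the margin is 0.20 × 7.69 = 1.538, which the article rounds to 1.5.

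**Shift from the asymmetric rule.** Let both arms truly have mean 7.69. Removing a fraction q of zero-VFD patients from the antibiotic arm gives a per-protocol mean of 7.69/(1 − q), while watchful waiting stays at 7.69. The spurious difference is 7.69/(1 − q) − 7.69.

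| q (assumed) | Antibiotic-arm mean | Shift against watchful waiting | Share of 1.538 |
|---|---|---|---|
| 2% | 7.85 | 0.16 | 10% |
| 5% | 8.09 | 0.40 | 26% |
| 10% | 8.54 | 0.85 | 56% |
| 15% | 9.05 | 1.36 | 88% |

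The whole margin would be used up when 1 − q = 7.69/9.228, that is q = 16.7%. If adherent deaths are kept in both arms, the shift is zero.

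**Effect on the conclusion.** A simulation used identical arms, 265 per arm, a zero-inflated scaled beta outcome with mean 7.69 and SD 10.67, and 4,000 runs. The chance of showing noninferiority against 1.538 days, intention-to-treat versus per-protocol, was 51% v 44% (q = 2%), 50% v 33% (5%), 49% v 17% (10%) and 52% v 8% (15%). Against a ratio margin of 0.8 it was 58% v 52%, 57% v 41%, 56% v 25% and 60% v 13%. The intention-to-treat figures on the day scale sit near 50% rather than 80% because the 295 rests on the log-scale ratio. That is a separate matter; the comparison within each pair is what counts here.

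**Size against sampling error.** The standard error of the difference is about 10.67 × √(2/265) = 0.93 VFD. The shifts of 0.16, 0.40, 0.85 and 1.36 are therefore about 0.2, 0.4, 0.9 and 1.5 standard errors. This ignores the slightly smaller per-protocol set, which would lower these ratios a little.

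**Counter-movement.** The same rule also makes deviators of antibiotic-arm patients who are discharged alive before completing the course, or who improve and stop before day 5. These patients probably have above-average VFDs. Excluding one patient with v VFDs offsets (v − 7.69)/7.69 excluded deaths, which is at most (28 − 7.69)/7.69 = 2.6. The article does not allow their number to be estimated.

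**The case against.** The strongest reply is that the decisive step is not in the text. No sentence says that deviators are deleted from the per-protocol set. The deviation criteria are to be adjudicated by the coordinating center, and the Discussion's wording suggests that the list may not be exhaustive. The statistical analysis plan or supplement could exempt deaths. This stands as a limit on certainty. It does not dispose of the point, because the article does more than stay silent: it states the rule together with an explicit exception, the exception leaves out death, and the rule is tied to the per-protocol analyses.

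It is also fair that the assumed mortality may be too high. Eligibility excludes hemodynamic instability, patients unlikely to survive beyond 48 hours and those with expected limitation of life support within 7 days. At 2% the shift is only about a tenth of the margin. Early discharges and early stoppers pull the other way, and watchful-waiting patients given antibiotics without a clear indication would also leave the set, so the net direction cannot be fixed from the article.

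Three stronger readings are tempting, and the documents do not support them.

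- A reader might infer that the noninferiority claim depends on this analysis. It does not. The decision rests on intention-to-treat, no rule requires both analyses to agree, the article argues that intention-to-treat may be the more conservative choice in antimicrobial trials, and an instrumental-variable analysis is also planned.
- A reader might infer that the per-protocol analysis would show watchful waiting to be inferior. Even at 15% the expected shift is at most about 1.5 standard errors. At 5%, the chance of a two-sided 5% result against watchful waiting is about 6%, against a nominal 2.5%. Failing to show noninferiority is not the same as showing inferiority.
- A reader might infer a risk of a false noninferiority claim. The death-related bias runs against watchful waiting, so by itself it cannot produce one.

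**Conclusion.** The point holds in a limited form. As written, the rule treats the same event, death while following the assigned strategy, as a deviation in one arm and as adherence in the other. If deviators are excluded, the per-protocol contrast between identical arms shifts against watchful waiting by 0.16 to 1.36 VFD for early mortality of 2% to 15%, about 10% to 88% of the 1.54-day margin.

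This rests on two assumptions: that deviators are excluded, which is implied but not stated, and the mortality range, for which the article gives no figure. The range counts deaths alone; the opposing effect of excluded early discharges and early stoppers is unknown. The primary analysis is untouched. The consequence is that the primary sensitivity analysis can wrongly fail to support a valid intention-to-treat result. The rule should be corrected before the analysis, but it is not a threat to the trial's main conclusion.

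**What to change.** For the per-protocol analysis, judge adherence only while the patient is alive and in hospital during the 7-day window. In both arms, count as adherent any patient who followed the assigned strategy until death or discharge. State explicitly in the statistical analysis plan whether deviators are excluded from the per-protocol set.

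This changes only an analysis definition, not how patients are managed. It costs about a sentence in the deviation criteria and a matching one in the statistical analysis plan, before database closure. Daily antibiotic use is already collected to day 28, and death and discharge are already needed for the outcomes. Censoring at deviation with inverse-probability weighting is an option the trial team could consider. It would take more specification and possibly more time-varying data than the article lists, and it is not part of the required change.

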### Trial outcomes

The primary outcome is VFD at 28 days. Ventilator-free days are defined as being free of IMV for at least 48 hours (successful extubation).^(24)^ If the patient is reintubated within 48 hours of extubation, this interval will be treated as zero VFDs. If reintubation is needed after 48 hours, this period will be counted as the VFDs. Patients who undergo a tracheostomy will be considered free of mechanical ventilation once they tolerate continuous nebulization (with or without oxygen), allowing for short periods (< 1 hour/day) of positive pressure ventilation. Patients who are discharged from the hospital alive before 28 days will be considered alive and free of mechanical ventilation at 28 days. Nonsurvivors up to 28 days will be considered to have zero VFDs.

The secondary outcomes are VAP-free survival at 28 days (key secondary outcome), all-cause mortality at 28 days, VAP incidence at 14 and 28 days, number of ICU-free days at 28 days, number of antibiotic-free days at 28 days, change in the Sequential Organ Failure Assessment (SOFA) score between randomization and 7 days and cumulative incidence of microbiologically isolated MDR bacteria at 28 days. Secondary safety outcomes are the incidence of culture-positive hospital-acquired infections at 28 days and severe adverse events at 28 days.

The VAP outcome will be adjudicated by at least two adjudicators who are blinded to the trial’s intervention and who have experience in the care of critically ill mechanically ventilated patients. If discrepancies arise, they will be resolved by consensus between both adjudicators. If no consensus is reached, a third adjudicator will be responsible for making a final decision on the diagnosis of VAP.

Detailed information on the outcomes and trial definitions is available in the Supplementary Material.

### Data collection

Patient data will be collected through an online case report form (e-CRF) using REDCap,^(25,26)^ developed by the data management team of Hospital Sírio-Libanês. Access to the e-CRFs will be password-protected and supported by the trial data management team.

Demographic and baseline data, including the Simplified Acute Physiology Score (SAPS) 3, laboratory data, data on physiological variables, previous antibiotic use, and use of steroids upon randomization, among others, were collected for all participants. Daily data on antibiotic utilization, microbiological cultures, and ventilatory support were collected for up to 28 days. Additional information on the data collection is available in the Supplementary Material.

### Data monitoring

A designed centralized data manager will perform the data monitoring for quality and completeness. Source data will also be routinely audited online or on-site according to a predefined procedure. During data collection, fields were explicitly designed to allow high-quality data to be collected using ranges and validation criteria. Further details on the data monitoring are described in the Supplementary Material.

### Adverse events

This is a trial in critically ill patients, and we acknowledge that, due to their clinical status, there is an inherent high risk of death and of several laboratory abnormalities, vital sign abnormalities, and symptoms directly related to the underlying illness severity, as well as usual treatment practices in ICUs. Therefore, these abnormalities will not necessarily be considered adverse events unless there is a suspicion or confirmation that they are related to the trial interventions.^(27)^ All severe adverse events potentially causally related to the trial intervention will be reported and investigated per GCP guidance.

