### Randomization, allocation concealment, and blinding

Patients will be randomized in a 1:1 ratio to each treatment arm (Watchful Waiting Group *versus* Antibiotic Treatment Group for 7 days). Randomization lists will be generated by an independent statistician using R software^(22)^ in random block sizes to preserve allocation concealment and will be stratified by center and by suspected diagnosis of viral pneumonia. Randomization will be performed using a central online randomization system (RedCap) that is available 24 hours a day.

This is an open-label trial in which both patients and investigators are not blinded to the interventions, given the nature of the trial and the need to follow local treatment regimens based on local microbiology. The adjudicators and trial statisticians will be blinded to the treatment assignment.

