For the outcomes including VAP as a secondary outcome, we will perform sensitivity analyses based on the definition of VAP, including the more specific and more sensitive definition of VAP (including possible and probable cases of VAP). These definitions are presented in the Supplemental Material.

All secondary analyses will follow the usual superiority framework for analysis. Further details on the statistical model for the primary outcome, secondary outcomes, sensitivity and subgroup analyses, and data presentation will be described in detail in the statistical analysis plan to be published before database closure, in accordance with international recommendations for reporting randomized clinical trials.

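### Severe adverse events are compared between arms, but the only stated rule for counting them turns on suspected relation to the intervention, which leaves the comparison open to differential attribution in an open-label trial

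*Protocol article*

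**What the plan says.** Four parts of the Protocol article bear on this.

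- *Trial outcomes*: "Secondary safety outcomes are the incidence of culture-positive hospital-acquired infections at 28 days and severe adverse events at 28 days". Relatedness is not a condition here.
- *Statistical analysis*: "All secondary analyses will follow the usual superiority framework for analysis". The safety outcomes are listed among the secondary outcomes, so severe adverse events are to be compared between groups.
- *Adverse events*: after noting that critically ill patients have many abnormalities from their illness and from usual ICU care, the article says that "these abnormalities will not necessarily be considered adverse events unless there is a suspicion or confirmation that they are related to the trial interventions". It then adds: "All severe adverse events potentially causally related to the trial intervention will be reported and investigated per GCP guidance".
- *Randomization, allocation concealment, and blinding*: "This is an open-label trial in which both patients and investigators are not blinded to the interventions". It also says "The adjudicators and trial statisticians will be blinded to the treatment assignment", but the only outcome that *Trial outcomes* assigns to adjudicators is VAP: "The VAP outcome will be adjudicated by at least two adjudicators who are blinded to the trial’s intervention".

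For outcome definitions and data collection the article refers to the Supplementary Material, which is not at hand.

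**The concern.** A causality filter is sensible for deciding which events in an ICU population need prompt reporting and investigation. It is a poor basis for a compared outcome, because the count then depends on a judgement that can differ by arm.

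Here the judgement is not symmetrical. In the Antibiotic Treatment Group, an event related to the intervention is mainly a drug effect. In the Watchful Waiting Group there is no study drug, so a related event must be a consequence of leaving VAT untreated. A rash or renal injury is easily put down to an antibiotic. Deterioration without antibiotics may be put down to the underlying illness, or blamed on the strategy by a clinician who favours treatment. The Discussion itself acknowledges that clinicians hold strong views on antimicrobials and usually lean towards using them.

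At stake is the reading of one secondary safety outcome. A difference in counted events could reflect attribution habits, and a real difference could be hidden by them. This matters most for antibiotic toxicity and non-infectious harm, which the other outcomes cover only in part.

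**Working it through.** The article gives no severe adverse event rate and no attribution figure, so there is no stated result to reproduce. The check is first a reading of the text, then an illustration with assumed inputs.

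**Reading**

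1. Outcome: severe adverse events at 28 days, unqualified (*Trial outcomes*).
2. Use: between-group superiority analysis (*Statistical analysis*).
3. Ascertainment: the one rule stated (*Adverse events*) has two parts. The first governs what is considered an adverse event, for abnormalities tied to illness or usual care. The second governs which severe events are reported and investigated. Both turn on suspected relation to the intervention.
4. Safeguard: none is stated for this outcome. Investigators are unblinded, and blinded adjudication is named for VAP only.

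The first part of step 3 goes beyond expedited reporting, because it concerns whether an abnormality counts as an adverse event at all. An unqualified outcome is thus paired with a causally filtered rule.

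**Illustration**

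Inputs: 295 per group (*Sample size*). The true severe event risk, equal in both arms, and the probability that an event is judged related are both assumed. The model takes the extreme case in which only events judged related are counted:

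counted risk = true risk × probability judged related.

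*Example A*, true risk 30%:

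- 20% judged related in one arm: 295 × 0.30 × 0.20 = 17.7, about 18.
- 40% in the other: 295 × 0.30 × 0.40 = 35.4, about 35.
- Pooled proportion = 53/590 = 0.0898; standard error = √(0.0898 × 0.9102 × 2/295) = 0.0235.
- z = (35 − 18)/295 ÷ 0.0235 = 2.45, two-sided p = 0.014.
- With 25% against 40%: 22 versus 35, z = 1.81, p = 0.07.

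*Example B*, chance of a false two-sided p < 0.05 with 295 per arm. The formula is Φ((|d| − 1.96·SE₀)/SE₁), where d is the difference in counted risks, SE₀ the pooled and SE₁ the unpooled standard error.

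| Judged related, antibiotic / watchful waiting | Counted risk ratio (watchful / antibiotic) | True risk 10% | 20% | 30% |
|---|---|---|---|---|
| 30% / 10% | 0.33 | 41% | 70% | 87% |
| 30% / 20% | 0.67 | 12% | 20% | 28% |
| 20% / 20% | 1.00 | 5% | 5% | 5% |
| 10% / 30% | 3.0 | 41% | 70% | 87% |

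One cell in full, for true risk 30% and 30% / 10%: counted risks are 0.09 and 0.03, so d = 0.06. SE₀ = √(2 × 0.06 × 0.94/295) = 0.01955 and SE₁ = √((0.0819 + 0.0291)/295) = 0.01940. Then (0.06 − 1.96 × 0.01955)/0.01940 = 1.12, and Φ(1.12) ≈ 0.87.

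The result runs from no distortion to a large one, in either direction, depending on inputs that the article does not supply.

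**The case against.** The strongest answer is that a reporting rule is being mistaken for an outcome definition. The outcome as listed has no causality condition. The sentence on severe events concerns reporting and investigation, for which such a filter is acceptable. The sentence on abnormalities says only that they will not necessarily count, and it covers abnormalities linked to illness or ICU care. Operational definitions and e-CRF rules are deferred to the Supplementary Material, which may already provide arm-neutral capture.

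Much of this stands, and it rules out three stronger statements that a reader might infer:

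- *That severe events are recorded only when judged related.* The article contains no bar on recording unrelated events.
- *That unblinded investigators make the causality judgement.* This is a plausible inference from the open-label design, but no assessor is named.
- *That the comparison is biased.* Differential attribution is possible, not shown. The illustration only shows that unequal attribution gives unequal counts.

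The impact is also bounded. All-cause mortality, VAP, SOFA change, culture-positive hospital-acquired infection, isolation of MDR bacteria and ICU-free days carry no causality condition. SOFA change to day 7 would pick up some renal injury. The primary outcome and the interim stopping rule both use ventilator-free days and do not depend on this count.

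What the objection does not remove is the mismatch. The article names a compared outcome without a relatedness condition, and the one rule it states for counting events makes relatedness matter. That is a feature of the stated text, not merely missing detail.

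**Conclusion.** The point holds in limited form. Severe adverse events are a between-group safety outcome. The only ascertainment rule in the article depends in part on suspected relation to the intervention, and no blinded assessment is stated for it. The comparison is therefore open to differential attribution bias.

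Direction and size cannot be determined. Under the assumptions shown (true risk 10% to 30%, attribution probabilities 10% to 30%, only related events counted), the chance of a spurious significant difference runs from the nominal 5% to about 87%. The upper end needs a threefold gap in attribution. If the Supplementary Material already counts severe events in both arms regardless of cause, the concern reduces to a sentence of clarification.

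This should be corrected because the remedy is cheap and the safety comparison would otherwise be hard to interpret. It does not threaten the primary conclusion.

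**What to change.** Reconcile *Trial outcomes* with *Adverse events*:

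1. State that the causality filter applies to expedited reporting and investigation only.
2. For the compared outcome, prespecify a short list of severe events covering harms expected from antibiotics and from withholding them. Record these in both arms to day 28 whatever the suspected cause.
3. Show judged relatedness by arm as a descriptive column, and say who judges it.

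If arm-neutral capture is not feasible for patients already enrolled, relabel the outcome as *severe adverse events judged related to the intervention*, report it descriptively, and draw no superiority conclusion from it.

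The cost is a few added e-CRF fields, which fit the daily collection to day 28 already planned, and a short protocol clarification. The article reports more than 180 patients included at the time of writing, so some back-entry from charts would be needed. It should use the same list and procedure in both arms so that it does not introduce a new imbalance.
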